**Time Line**

Results are expected by the end of 2010.

**NOTES**

*Pneumonia score:*

A set of 10 items from a list of 20 possible questions will be selected at each study site (based on what local doctors / researchers consider to be most culturally appropriate and based on the findings of the pilot study - selected by the local PI based on level of comprehension by caregivers, performance in comparison to known diagnoses and the informed opinion / experience of the local PI). This list represents symptoms and signs of pneumonia which are of increasing severity. The interviewer will ask the caregiver about the presence of each specific sign separately, and record her responses. The clinical signs are:

- Cough
- Fever
- Sweating
- Irritability
- Fatigue
- Restlessness
- Fast breathing
- Shortness of breath
- Loss of appetite
- Decreased water intake / drinking
- wheezing
- Chest pain
- Difficulty breathing
- Intercostal or subcostal retractions
- Flared nostrils
- Grunting
- Repeated vomiting
- Cyanosis
- Haemoptysis / blood when child coughs
- Fits

*Video clips*

During the interview, the research worker will show the caregiver a short video clip showing a child suffering from pneumonia, followed by a clip showing a child with a “cough or cold”. The videos will show clinical signs commonly associated with both, and the mother will be asked which clip most accurately shows the signs her child was displaying when they were ill. The research worker will record whether the caregiver selected the child with pneumonia, or the child with “cough or cold”.

- Child with signs of pneumonia: clinical signs of pneumonia (fast breathing of at least 10-15 breaths /minute above the threshold for that age and /or chest indrawing)
- Child with signs of “cough or cold”: (blocked or runny nose and noisy upper respiratory breathing but NO fast breathing at least 10 breaths /minute below the age threshold)

There should be a video made of a 2 month old child and a 2 year old child for both pneumonia and “cough and cold”. An alternative to be explored in the pilot study is to make separate videos of children with “cough and cold”, pneumonia (fast breathing) and severe pneumonia (chest indrawing). The research worker should select the age category that will best represent the child which is being recruited and show the relevant clips to the mother.

*Drug Chart*

During the interview, the research worker will show the caregiver a chart which will contain pictures of all the locally used medications. The research worker will ask the caregiver which, if any, of these treatments her child received. This drug chart should be presented both as a separate laminated sheet and loaded onto the study laptop PC to be displayed after the video is shown. The drugs shown should be clearly displayed, with any identifying marks (e.g. markings) easily visible. The caregiver will also be asked about details of dose and duration of treatment given and source of the medication. The pilot study will consider methods proposed in the WHO manual edited by Hardon before the final study protocol is established.

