All children will then be treated according to the standard management protocols of that particular clinic. It is expected that some of the study children with pneumonia will go on to develop severe pneumonia, and require hospital referral. If this should happen the local health worker will ensure that the child is referred to the nearest health facility to receive medical care. A detailed record of the treatment given to the caregiver will be recorded.

It is recognized that children attending a clinic with pneumonia could represent a biased group that are not fully representative of all sick children. We will collect DHS data on socio-economic status in order to compare the sample population to a wider population. Furthermore, it is possible that the consent process and information sheet may introduce a source of bias in the recording of recall of symptoms and events.

*Follow up at home*

The primary caregivers of these children will first be interviewed using the DHS and MICS questions relating to pneumonia (see Annex) either at 2 weeks (200 with pneumonia and 200 with cough or cold) or 4 weeks (100 with pneumonia and 100 with cough or cold) after diagnosis. This will follow the DHS and MICS procedures as closely as possible. The order of administering the DHS and MICS questionnaires will be alternated with each child so that each is administered first on 50% of occasions. After this is completed they will then also be questioned about specific signs of pneumonia (which will form a pneumonia score - see below) and will be asked to watch a video of a child suffering from pneumonia and of a child suffering from an upper respiratory infection (asking which best represents their child’ respiratory illness episode). Finally, a drug chart will then be used to show them pictures of locally used medicines with a request to identify which medicines, if any, their child was prescribed. These research workers should be given the address details of the child but not be made aware of the study group of the child nor have access to the clinical details of the child recorded at recruitment.

*Home visit interview sequence:* The research worker will

1. introduce him/herself to the caregiver, and check that the details match those on the recruitment form.
2. inform the mother of the interview process and ensure that she is willing to participate (and obtain written consent).

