3. check that the child’s details are correct, and make sure that the caregiver understands that the interview only concerns this child, and that she should only answer the questions in relation to this child.
4. start by asking the DHS questions (Annex 1) then ask MICS questions (Annex 2) – this sequence will be alternated from child to child to that DHS is asked first in 50% of children
5. ask pneumonia score questions (Annex 3)
6. show the caregiver the video clips and ask mother to identify which disease best represents her child
7. show the caregiver a drugs chart and ask her to identify with what her child was treated; note whether treatment information is based on this or actual observation of medications in the home
8. ask if the mother has a pharmacist’s note or a ‘road to health’ card, and record any information from the past 2 or 4 weeks.

*Study analysis*

The study report will include a detailed description of the epidemiological and health services characteristics of the study population

There will be 4 separate groups interviewed in this study:

- Mother’s whose child has been accurately diagnosed as having pneumonia (or severe pneumonia if this is treated in the community) by a physician, and is interviewed after 2 weeks.
- Mother’s whose child has been accurately diagnosed as having pneumonia (or severe pneumonia if this is treated in the community) by a physician, and is interviewed after 4 weeks.
- Mother’s whose child has been accurately diagnosed as not having pneumonia by a physician, and is interviewed after 2 weeks
- Mother’s whose child has been accurately diagnosed as not having pneumonia by a physician, and is interviewed after 4 weeks

Data from the interviews and the clinical case study forms will be used to calculate sensitivities and specificities of each of the above methods (DHS / MICS defined pneumonia; pneumonia defined by various pneumonia score thresholds; video-assisted recognition of pneumonia) for the diagnosis of pneumonia and for antibiotic treatment. These will be estimated for all possible pneumonia score thresholds so that an optimum performance threshold can be defined for the score. The caregiver will then be asked to show the research worker any pharmacist’s note, ‘road to health’ card or other health record which may have details of the illness and treatment given.

*Sensitivity + specificity calculations:*

|  | | **Medical diagnosis of Pneumonia** | | |
| --- | --- | --- | --- | --- |

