**Study organization and management**

**Study Management**

[name] will have overall responsibility for the study. He will be assisted by [name], who will conduct initial visits to each site to finalize the study protocol and ensure data quality and comparability across sites, and a follow-up visit to each site shortly after data collection begins. [name] [name] and [name] will be responsible for managing the day-to-day activities and conducting the primary analysis.

*Site specific preparation before recruitment*

*Ethical approval*

This will be sought from the appropriate authorities at each study sites and WHO Ethics committee. Each site will be responsible for preparing study recruitment, follow up and consent forms in the local language and for obtaining local ethical approval.

*Producing a pneumonia video*

Each site will be required to produce a video (at least 2 minute clip) of at least one child displaying the clinical signs of pneumonia (fast breathing of at least 10 breaths/minute above the threshold for that age and lower chest indrawing ) and at least one child demonstrating signs of “cough or cold” (blocked or runny nose and noisy upper respiratory breathing but NO fast breathing at least 10 breaths /minute below the age threshold) and upload it onto the study PC (or DVD player) with a medium sized screen that will be used for the interviews. There should be a video made of a 2 month old child and a 2 year old child for both pneumonia and “cough and cold”. The pilot test of the video will check that the video quality is appropriate for the study so that poor quality does not give falsely poor results.

*Developing a pneumonia score*

The pilot study will include a check of the face validity and cultural appropriateness of the items in the study protocol together with some formative research to identify local and commonly used terms for some of the items in the list, e.g. restlessness, flared nostrils, irritability etc.

*Identifying and documenting local treatments*

Each study site will also be required to document all drugs which are commonly used in that area to treat pneumonia, malaria and other febrile illnesses. They will also be required to take pictures of the individual pills/syrups/injections, which will then either be loaded onto the study PC, or printed on to a “pill board”.

*Training*

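### Clip order is fixed with the pneumonia clip first, and the protocol's sections conflict on drug-chart format and on the content of the pneumonia clip

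*Protocol*

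**What the plan says.** **Clip order.** Protocol, NOTES, Video clips: the worker "will show the caregiver a short video clip showing a child suffering from pneumonia, followed by a clip showing a child with" cough or cold, and then "the mother will be asked which clip most accurately shows the signs her child was displaying when they were ill". The Follow up at home section names the clips in the same order: the caregiver "will be asked to watch a video of a child suffering from pneumonia and of a child suffering from an upper respiratory infection". Neither place varies the order. The same section, and step 4 of the home visit sequence, alternate DHS and MICS from child to child so that each comes first half the time.

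**Drug chart.** The Project research questions ask for sensitivity and specificity with a paper board and with a computer board. Three places describe how the chart is used:

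- NOTES, Drug Chart: "This drug chart should be presented both as a separate laminated sheet and loaded onto the study laptop PC".
- Identifying and documenting local treatments: pictures are taken "which will then either be loaded onto the study PC, or printed on to a" pill board.
- Home visit interview sequence, step 7: "show the caregiver a drugs chart and ask her to identify with what her child was treated", with no format named.

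**Clip content.** Producing a pneumonia video requires fast breathing "above the threshold for that age and lower chest indrawing". NOTES, Video clips, requires fast breathing "above the threshold for that age and /or chest indrawing". Each site makes its own video, and the text after Table 2 says that results will be summarised over all sites.

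**The concern.** Video-assisted recognition is a named research question and a project outcome, reported as sensitivity and specificity. The caregiver makes a two-way choice, and position is tied completely to diagnosis: the first clip is always pneumonia and the last is always cough or cold. A caregiver who is unsure and leans towards whichever clip came last (or first) therefore gives an answer that counts as a diagnosis. Such a lean would raise one of the two measures and lower the other. Nothing in the collected data could show that this had happened.

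For the chart, separate estimates by format require knowing which format produced which answer, and whether the caregiver had already seen the other one. For the clips, two definitions allow sites to show different stimuli while each follows some part of the protocol. The pooled video result would then mix two tests. All three are rules of data collection, so a later analysis plan cannot repair them.

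**Working it through.** The plan gives no figure for any of these effects, so there is none to reproduce.

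**1. Clip order**

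Inputs: sensitivity (Se) 60% and specificity (Sp) 70%, the lower ends of the baseline ranges in Sample size calculation (given there for the survey measures generally, not for the video). The share *b* of caregivers who choose by position is an assumption.

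With the pneumonia clip always first:

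- last-clip preference: Se' = (1−b)Se and Sp' = (1−b)Sp + b
- first-clip preference: Se' = (1−b)Se + b and Sp' = (1−b)Sp
- order alternated 50:50: Se' = (1−b)Se + b/2 and Sp' = (1−b)Sp + b/2

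| b (assumed) | Last-clip preference, Se/Sp | First-clip preference, Se/Sp | Alternated, Se/Sp |
| --- | --- | --- | --- |
| 5% | 57 / 71.5 | 62 / 66.5 | 59.5 / 69 |
| 10% | 54 / 73 | 64 / 63 | 59 / 68 |
| 20% | 48 / 76 | 68 / 56 | 58 / 66 |

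At the upper ends of the ranges (70%/90%) with b = 10%, the values are 63/91, 73/81 and 68/86.

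Under the fixed order, an observed 54/73 fits a true 60/70 with b = 10% and a last-clip preference. It fits equally well a true 54/73 with no position effect. The data cannot tell these apart.

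Under alternation, the two orders differ by b in each measure: 64 − 54 = 10 in sensitivity and 73 − 63 = 10 in specificity. So b can be estimated, with limited precision:

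- Sensitivity, one site, 150 children per order: 1.96 × √[(0.64×0.36 + 0.54×0.46)/150] = 1.96 × √0.003192 = ±11.1 points.
- Averaged with the specificity difference (variance (0.73×0.27 + 0.63×0.37)/150 = 0.002868): 1.96 × √[(0.003192 + 0.002868)/4] = ±7.6 points.
- Over two sites: 7.6/√2 = ±5.4 points.

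**2. Drug-chart format**

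| Place | Format | Consequence for an estimate by format |
| --- | --- | --- |
| NOTES, Drug Chart | both | Paired answers are possible, but no order of formats and no separate recording is stated |
| Identifying and documenting local treatments | either | No rule says who sees which; format could follow site or interviewer |
| Home visit sequence, step 7 | one chart, unnamed | The answer cannot be attributed to a format |

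If both formats are shown in alternated order, each is seen first by about 300/2 = 150 children per diagnosis group per site. Half-widths, 1.96 × √[p(1−p)/n]:

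| p | n = 150 (first-seen) | n = 300 (all answers) |
| --- | --- | --- |
| 60% | ±7.8 | ±5.5 |
| 70% | ±7.3 | ±5.2 |

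The denominators for drug recall are children who did or did not receive the drug, not the diagnosis groups. These figures are a guide only if treatment groups are of similar size to diagnosis groups.

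**3. Clip content**

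Under the site-preparation text every pneumonia clip shows both signs. Under NOTES a clip with one of the two suffices. The fast-breathing margin also differs: at least 10 breaths per minute above threshold in one place, at least 10 to 15 in the other. A clip without indrawing would satisfy NOTES and breach the site-preparation text.

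**The case against.** A reader might infer that the video estimates *are* biased. The documents do not support that: they give no evidence that a position preference exists, nor of its direction or size, and every value of b above is assumed. It can also be argued that the two clips form one test, so that a fixed order belongs to the tool and its accuracy is that of the tool as administered. DHS and MICS are two competing instruments with closely similar questions, which makes alternation more pressing there. Alternation would not recover the true values either (59/68 against 60/70). All of this stands. It limits the claim, but it does not remove the case for a cheap safeguard that makes the effect visible.

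A reader might also infer that the paper and computer question cannot be answered, or that format equals site. Both go too far. The research question asks for an estimate with each board, not a head-to-head test. NOTES can be read as showing both formats to every caregiver, a paired design that needs no allocation by child. The either/or text does not say that the choice is made by site. Step 7 does not limit the caregiver to one answer, and Annex 5 is still to be completed.

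Finally, parts are left open to the pilot: chart methods, final forms, and the option of separate clips for fast breathing and for indrawing. Site visits are meant to secure comparability. But none of the pilot tasks described covers clip order or a format rule, and the conflicting sentences still need one resolution.

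**Conclusion.** The point holds in three limited parts.

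- **Clip order.** It is fixed and followed by a two-way choice. Any position preference would shift sensitivity and specificity in opposite directions, undetected. Under the assumed 10% the shift is 5 points either way from the alternated values, the same as the ±5% precision the plan aims for. The true size may be nil.
- **Chart format.** Three places conflict, so separate estimates for the two boards have no clean route as written. Confounding with site or interviewer is a risk under one reading, not a fact.
- **Clip content.** Two definitions conflict. Different clips at different sites are possible, not shown, but results are to be summarised over sites.

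These should be settled before the forms and videos are final.

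**What to change.** 1. **Clip order.** Alternate it child by child, by visit list and without reference to diagnosis, and record it on the home follow-up form. Cross it with the DHS/MICS order and the chart-format order (2 × 2 × 2 = 8 sequences, rotated), so that the alternations do not run in step. Report video accuracy overall and by clip order. The cost is one field and a printed rota. The order effect will be estimated only to about ±11 points for sensitivity at one site.
2. **Drug chart.** Make the three places agree. Show both formats to each caregiver in alternated order, record a separate answer for each, and record which came first. Use all answers for the estimate by format, and first-seen answers as a check for carry-over. State that the check rests on about 150 children per diagnosis group per site (about ±7 to 8 points at 60–70%), which is wider than the ±5% target. The cost is extra interview time and added fields on a form not yet completed.
3. **Clip content.** Reconcile the site-preparation text and NOTES to one definition, covering both the signs and the breathing-rate margin, and use it at every site. If the pilot leads to separate clips by severity, state the same set for all sites. The cost is an edit, provided it is made before filming.

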**Annexes:**

**Annex 1: DHS(V) questions – these will be replaced by the MEASURE DHS phase III questions (in related document “Copy of DHS6 Woman's QRE 16 March pneumonia-1”**

533 *Has (NAME) been ill with a fever at any time in the last 2 weeks?*

*Yes 1*

*No 2*

*Don’t Know 8*

1. *Has (NAME) had an illness with a cough at any time in the last 2 weeks?*

*Yes 1*

*No 2*

*Don’t Know 8*

1. *When (NAME) had an illness with a cough, did he/she breathe faster than usual with short, rapid breaths or have difficulty breathing?*

*Yes 1*

*No 2*

*Don’t Know 8*

1. *Was the fast or difficult breathing due to a problem in the chest or to a blocked or runny nose?*

*Chest Only 1*

*Nose Only 2*

*Both 8*

*Other _______________ (Specify) 6*

*Don’t Know 8*

1. *Check 533: Had Fever?*
2. *Now I would like to know how much (NAME) was given to drink (including breastmilk) during the illness with a (fever/cough). Was he/she given less than usual to drink, about the same amount, more than usual to drink?*

*If less, probe: Was he/she given much less than usual to drink or somewhat less?*

*Much Less 1*

*Somewhat Less 2*

*About the Same 3*

*More 4*

*Nothing to Drink 5*

*Don’t Know 6*

1. *When (NAME) had a (fever/cough), was he/she given less than usual to eat, about the same amount, more than usual, or nothing to eat?*

*If less, probe: Was he/she given much less than usual to eat or somewhat less?*

*Much Less 1*

*Somewhat Less 2*

*About the Same 3*

*More 4*

*Stopped Food 5*

*Never Gave Food 6*

*Don’t Know 6*

1. *Did you seek advice or treatment for the illness from any source?*

*Yes 1*

*No 2*

1. *Where did you seek advice or treatment? Anywhere else?*

*Probe to identify each type of source and circle the appropriate code(s).*

*If unable to determine if a hospital, health center or clinic is public or private medical, write the name of the place.*

*(Name of place)*

*Public Sector*

*Govt Hospital A*

*Govt Health Center B*

*Govt Health Post C*

*Mobile Clinic D*

*Fieldworker E*

*Other Public F*

*________________ (specify)*

*Private Medical Sector*

*PVT Hospital/Clinic G*

*Pharmacy H*

*PVT Doctor I*

*Mobile Clinic J*

*Fieldworker K*

*Other Private Med. L*

*________________ (specify)*

*Other Source*

*Shop M*

*Traditional Practitioner N*

*Other X*

*________________ (specify)*

1. *Were did you first seek treatment? Use letter code from 541.*
2. *How many days after the illness began did you first seek advice or treatment for (NAME)? If the same day, record ‘00’.*
3. *Is (NAME) still sick with (fever/cough)?*

*Fever Only 1*

*Cough Only 2*

*Both Fever and Cough 3*

*No, Neither 4*

*Don’t Know 5*

1. *At any time during the illness, did (NAME) take any drugs for the illness?*

*Yes 1*

*No 2*

1. *What drugs did (NAME) take? Any other drugs? Record all mentioned.*

*Antimalarial Drugs*

*SP/Fansidar A*

*Chloroquine B*

*Amodiaquine C*

*Quinine D*

*Combination with Artemisinin E*

*Country Spec. CBD Antimalarial F*

*Other Antimalarial G*

*________________ (specify)*

*Antibiotic Drugs*

*Pill/Syrup H*

*Injection I*

*Other Drugs*

*Aspirin J*

*Acetaminophen K*

*Ibuprofen L*

*Other ________________ (specify) X*

*Don’t Know Z*

*Followed by specific questions about each drug mentioned…*

**Annex 2: MICS questions**

| CA7. At any time in the last two weeks, has (name) had an illness with a cough? | Yes 1  No 2  DK 8 | 2CA14  8CA14 |
| --- | --- | --- |
| CA8. When (name) had an illness with a cough, did he/she breathe faster than usual with short, rapid breaths or have difficulty breathing? | Yes 1  No 2  DK 8 | 2CA14  8CA14 |
| CA9. Was the fast or difficult breathing due to a problem in the chest or a blocked or runny nose? | Problem in chest 1  Blocked or runny nose 2  Both 3  Other (specify) 6  DK 8 | 2CA14  6CA14 |
| CA10. Did you seek any advice or treatment for the illness from any source? | Yes 1  No 2  DK 8 | 2CA12  8CA12 |
| CA11. FROM WHERE DID YOU SEEK ADVICE OR TREATMENT? |  |  |
| CA12. Was (name) given any medicine to treat this illness? | Yes 1  No 2  DK 8 | 2CA14  8CA14 |
| CA13. What medicine was (name) given?  Probe:  Any other medicine?  Circle all medicines given. Write brand name(s) of all medicines mentioned.    (Names of medicines) | Antibiotic  Pill / Syrup A  Injection B  Anti-malarials M  Paracetamol / Panadol / Acetaminophen P  Aspirin Q  Ibuprofen R  Other (specify) X  DK Z |  |

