**Annex 3:** **Pneumonia score questions**

*1 Has (name) suffered from a* ***cough*** *in the past (___) weeks?*

*2 Has (name) had a* ***fever*** *in the past (___) weeks?*

*3 Has (name) suffered form* ***chills or sweats*** *over the past (___) weeks?*

*4 Has (name) been* ***restless*** *over the past (___) weeks?*

*5 Has (name) been unusually* ***irritable*** *over the past (___) weeks?*

*6 Has (name) had any* ***loss of appetite*** *over the past (___) weeks?*

*7 Has (name) been* ***abnormally sleepy*** *or* ***difficult to wake*** *over the past (___) weeks?*

*8 Have you noticed (name) making a* ***wheezing*** *sound when he/she breathed over the last (__) weeks?*

*9 Has (name) appeared* ***short of breath*** *over the past (___) weeks?*

*10 Has there been a period over the past (___) weeks when (name) has seemed to be* ***breathing faster*** *than normal?*

*11 Have you noticed (name’s)* ***nostrils flaring*** *when he/she breathed over the past (___) weeks?*

*12 Has (name)* ***refused to drink*** *or had a definite* ***decrease in the amount of water he / she drank*** *over the past (___) weeks?*

*13 Did you notice that (name’s)* ***skin between their ribs, or his/ her tummy move inwards*** *when they breathed over the past (___) weeks*

*14 Did (name) seem to have any* ***chest pain*** *over the past (___) weeks?*

*15 Has there been a period over the last (___) weeks where (name) seemed to have* ***difficulty breathing****?*

*16 Has (name)* ***vomited*** *at all over the past (___) weeks?*

*17 Have you heard (name) making* ***grunting*** *noises during the past (___) weeks?*

*18 Has (name) appeared to have a slightly* ***blue coloration*** *to his/her skin, particularly their lips or tongue, over the past (___) weeks*

*19 Has (name)* ***coughed up any blood*** *over the past (___) weeks?*

*20 Has (name) had any* ***fits*** *overt the past (___) weeks*

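### At the 4-week interview the MICS opening question, and the DHS items as printed, still ask about the last two weeks, so the DHS/MICS recall comparison confounds elapsed time with question coverage

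*Protocol*

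**What the plan says.** Under Follow up at home, caregivers are interviewed either 2 weeks after diagnosis (200 pneumonia and 200 cough or cold per site) or 4 weeks after (100 and 100). On the DHS and MICS interviews the section says: "This will follow the DHS and MICS procedures as closely as possible".

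The look-back windows in the interview material are:

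- **MICS, Annex 2, CA7:** "At any time in the last two weeks, has (name) had an illness with a cough". The answers No and DK both route to CA14, past CA8-CA9 (breathing) and CA12-CA13 (medicine).
- **DHS, Annex 1, as printed:** "Has (NAME) had an illness with a cough at any time in the last 2 weeks". The fever item uses the same window. The annex title says of the printed items: "these will be replaced by the MEASURE DHS phase III questions".
- **Pneumonia score, Annex 3:** the window is a blank, as in "over the past (___) weeks".
- **Record check, Home visit interview sequence, step 8:** "record any information from the past 2 or 4 weeks".

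The comparison of 2-week with 4-week recall is a listed research question, one of the two considerations behind the sample size, and a project outcome in the Plan of Analysis. The sample size section treats a 10-point difference in sensitivity or specificity as programmatically important.

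**The concern.** In the 4-week group the illness to be recalled was seen at the clinic about 28 days before the interview. A two-week window opens about 14 days after that visit. If the child was well by then, No is the right answer to the question as worded.

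The 2x2 tables have no place for that. A pneumonia case with No goes into cell c and lowers sensitivity. A cough-or-cold case with No goes into cell d and raises specificity. Both shifts look like an effect of time on recall, and both would occur with perfect memory.

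Two further comparisons are affected. After No at CA7 the MICS medicine items are never asked, so a child who received an antibiotic is counted as not reported. And if the Annex 3 blank is filled with four, the score covers the clinic illness while DHS and MICS in the same interview do not, which favours the score. Analysis cannot recover answers that the skip prevented from being collected.

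**Working it through.** **1. The plan's own figure.** The text gives about 300 per group for a 10-point difference with 80% power. It states no alpha, so two-sided 5% is assumed. For 70% versus 80%, with pooled proportion 0.75:

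n = [1.96·√(2·0.75·0.25) + 0.8416·√(0.70·0.30 + 0.80·0.20)]² / 0.10² = (1.200 + 0.512)² / 0.01 ≈ 293.2, so 294 per recall group.

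This reproduces about 300 for equal groups. It is used here only to confirm that 10 points is the difference the study is built to see.

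**2. Model for the window effect.** Let Se and Sp be the values when the window covers the illness, and let q be the share of children with any cough in the last 14 days at the 4-week visit. Assume that memory is identical at both intervals, that caregivers of children inside the window answer as they would at 2 weeks, and that the others answer No. Then:

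- 4-week sensitivity = Se × q
- 4-week specificity = 1 − (1 − Sp) × q

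Se of 60-70% and Sp of 70-90% are the protocol's baseline ranges. The protocol gives no q, so it is shown over a range.

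| q | Se 60% becomes | Se 70% becomes | Sp 70% becomes | Sp 90% becomes |
|---|---|---|---|---|
| 1 | 60% | 70% | 70% | 90% |
| 0.9 | 54% | 63% | 73% | 91% |
| 0.75 | 45% | 52.5% | 77.5% | 92.5% |
| 0.5 | 30% | 35% | 85% | 95% |
| 0.25 | 15% | 17.5% | 92.5% | 97.5% |
| 0 | 0% | 0% | 100% | 100% |

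**3. When the artefact reaches 10 points.** The false drop in sensitivity is Se × (1 − q). Setting it to 0.10 gives q = 1 − 0.10/0.70 = 0.857 for Se 70%, and q = 1 − 0.10/0.60 = 0.833 for Se 60%. For specificity the rise is (1 − Sp)(1 − q). It reaches 10 points at q = 1 − 0.10/0.30 = 0.667 for Sp 70%, and only at q = 0 for Sp 90%.

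**4. Chance of a false finding.** With 200 versus 100 pneumonia cases at one site and no difference in memory, the probability of a significant difference in sensitivity (two-sided 5%) is:

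| q | Se 60% | Se 70% |
|---|---|---|
| 0.9 | 0.17 | 0.23 |
| 0.75 | 0.69 | 0.84 |
| 0.5 | 0.999 | above 0.999 |

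For Se 70% and q = 0.75, the pooled proportion is (140 + 52.5)/300 = 0.642 and the null standard error is √(0.642·0.358·(1/200 + 1/100)) = 0.0587. The standard error under the alternative is √(0.21/200 + 0.2494/100) = 0.0595. So z = (0.175 − 1.96·0.0587)/0.0595 ≈ 1.01, which gives 0.84.

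**5. Caregivers who ignore the window.** If only a share L of caregivers of recovered children answer literally, replace q by 1 − (1 − q)·L. With q = 0.5 and L = 0.5 the effective value is 0.75, so the q = 0.75 rows apply. The 10-point threshold is met once (1 − q)·L is about 0.14 (Se 70%) to 0.17 (Se 60%).

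**The case against.** The strongest reply is that the annexes are not the final instruments. The DHS text is to be replaced, the training section says forms are settled only after the pilot, and the home form in Annex 5 still has its DHS/MICS block to be added. The introduction uses recall period to mean a survey's look-back, so comparing two- and four-week recall periods may imply matching windows. The Annex 3 blank and the record check suggest the authors had this in mind, and the instruction to follow DHS/MICS procedures closely leaves room for adaptation.

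Much of this stands. The DHS half cannot be confirmed for the final form, and an unfinished form is a plausible explanation. But Annex 2 carries no replacement note, its wording is explicit, and no section tells anyone to change it. The interview step asking caregivers to answer only about this child fixes the child, not the dates.

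A reader might go further and infer that the recall comparison measures wording instead of memory, or that antibiotic recall at 4 weeks is lost altogether. The protocol supports neither. A child still coughing in the last 14 days correctly yields Yes, so time and window are confounded and memory still contributes. The video and drug chart are not tied to two weeks, and the score is not if its blank is filled with four. Only the MICS medicine items are shown to be skipped, because the printed DHS items give no skip rule after the cough question.

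**Conclusion.** The point holds for MICS as printed, and for DHS unless the replacement text differs. Followed as written, the 4-week group is asked about a period that need not include the illness being validated. That biases DHS/MICS sensitivity down, specificity up and MICS-based antibiotic recall down.

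The direction follows from the wording, the skip and the 2x2 tables. The size does not, because it rests on q and on how literally caregivers answer, and neither is in the protocol. If all answer literally and memory is unchanged, q of about 0.83-0.86 or lower is enough for a false drop of 10 points from a baseline of 60-70%. If q is close to 1, or most caregivers disregard the window, the effect is small. It should be settled before forms are final, since the comparison is a main objective and the skipped answers cannot be reconstructed.

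**What to change.** - In the 4-week group, set the look-back in MICS CA7, and in the fever and cough items of the final DHS text, to a window that covers the clinic visit: four weeks, with allowance for interviews a few days late.
- Apply the same allowance in the 2-week group. An interview on day 15 already puts the visit outside a two-week window.
- Fill the Annex 3 blanks with the number used for DHS and MICS in that interview.
- State in the protocol that the 4-week group tests DHS/MICS adapted to this window.

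The cost is a changed phrase on forms that are still open, and the sample size is unaffected. The downside is that the 4-week version departs from verbatim DHS/MICS wording, so its results describe an adapted instrument and not the surveys as printed. A test of four-week recall needs that departure in any case.
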